## Abstract

**Background:**

Acute coronary syndrome (ACS) is a life-threatening condition that requires rapid identification to prevent morbidity and mortality. Differentiating ACS from benign conditions remains difficult in out-of-hours primary care (OOH-PC) settings due to non-specific and overlapping symptom profiles, and limited diagnostic resources. Current guidelines promote a low threshold for emergency department (ED) referral. Despite this cautious approach, ACS cases are still missed. The arrival of high-sensitivity troponin (hs-troponin) point-of-care testing (POCT) may enable safer, faster, and more efficient diagnosis.

**Methods and analysis:**

This multicenter prospective diagnostic accuracy trial evaluates the *HEART-GP strategy*, combining a single fingerstick hs-troponin test with clinical assessment and optional ECG. Adults (≥18 years) presenting with acute chest pain or discomfort to one of four participating Dutch OOH-PC centers are eligible. The primary outcome is the occurrence of major adverse cardiovascular events a composite of death, ACS, or urgent revascularization within six weeks. Diagnostic safety (sensitivity, negative predictive value) and efficiency (ED referral reduction) will be compared against standard care. Secondary analyses will assess the value of sex-specific cut-offs and integration with existing risk scores.

**Anticipated results:**

We anticipate that the *HEART-GP strategy* will demonstrate improved diagnostic safety along with efficiency gains in OOH-PC. Our straightforward rapid rule-out strategy holds promise to be widely implemented in primary care settings to advance the evaluation of acute chest pain.

**Ethics:**

The study was approved by the Medical Research Ethics Committee of the Amsterdam UMC (NL82428.000.22, 02-03-2023) and registered in the ISRCTN-registry (ISRCTN11954040 https://doi.org/10.1186/ISRCTN11954040).

## Introduction

1

### Background and rationale

1.1

Acute coronary syndrome (ACS) is a life-threatening condition requiring timely recognition and treatment to prevent severe morbidity and mortality [1]. However its clinical presentation often overlaps with far more common non-cardiac conditions such as musculoskeletal or gastrointestinal disorders [[2], [3], [4]]. The primary diagnostic challenge is to distinguish life-threatening causes, like ACS, from more benign causes. This is particularly pronounced in healthcare systems where general practitioners (GPs) act as the 24/7 first point of contact for urgent care, yet have limited access to reliable diagnostic instruments/tools, such as cardiac troponin testing for detecting myocardial ischemia.

The hallmark symptom for ACS is chest pain, and in Dutch out-of-hours primary care (OOH-PC), GPs annually assess over 160.000 patients with chest pain (i.e. 9 per 1000 inhabitants), representing a substantial share of out-of-hours consultations, as chest pain is in the top 10 of ‘presenting complaints’ [5]. GP assessments rely on clinical judgement, physical examination, and, when available, an electrocardiogram (ECG). These tools may help identify alternative causes for ACS, or confirm ST-elevation, but are insufficient to safely rule out ACS [3]. To minimize the risk of missed ACS, Dutch GP guidelines recommend a low referral threshold [6], and GPs generally adhere to this recommendation, resulting in high referral rates (i.e. 40-70%) for patients with chest pain to the emergency department (ED) [3,7]. This cautious approach increases burden on ambulance services, ED workload, and healthcare costs, while also causing patient distress [8]. Despite high referral rates, 8-19% of ACS cases are initially missed [7,9,10], suggesting that the current assessment strategies in Dutch (OOH-) primary care remain suboptimal, failing to guarantee diagnostic safety while also compromising efficiency.

The development of high-sensitivity troponin (hs-troponin) point-of-care testing (POCT) may constitute a paradigm shift by bringing a rapid, user-friendly and reliable diagnostic rule-out instrument to pre-hospital care. Studies in EDs demonstrated a high diagnostic accuracy of hs-troponin POCT, showing that a single low-level troponin measurement can effectively rule-out ACS [11]. However, these findings may not translate directly to primary care, where ACS prevalence is lower, diagnostic protocols are less standardized, and patient characteristics and work flows differ substantially from hospital settings.

### Objectives

1.2

To address this gap, we are conducting a diagnostic trial evaluating a primary care-tailored approach for ruling out ACS in OOH-PC that balances diagnostic safety and efficiency. Our primary objective is to evaluate the diagnostic performance of the *HEART-GP strategy*, which integrates a single fingerstick-obtained hs-troponin measurement with clinical assessment and an optional ECG, in terms of safety (sensitivity and negative predictive value) and efficiency (reduction in ED referrals) when used in out-of-hours primary care. The primary outcome is major adverse cardiovascular events (MACE), a composite of death, ACS, or urgent revascularization within six weeks of index presentation, reflecting the risk for cardiovascular events rather than a single clinical syndrome.

The secondary objectives are:1.To compare the diagnostic performance (safety and efficiency) of the *HEART-GP strategy* with current standard care based on (unaided) clinical judgment.2.To evaluate whether using sex-specific versus universal hs-troponin cut-off values improves safety and/or efficiency.3.To assess whether embedding hs-troponin measurements in established clinical risk scores (HEART, INTERCHEST, Marburg Heart Score) further improves diagnostic performance compared to the HEART-GP strategy alone.

### Anticipated results

1.3

We anticipate that the *HEART-GP strategy* will demonstrate improved diagnostic safety along with efficiency gains in OOH-PC. Our straightforward rapid rule-out strategy holds promise to be widely implemented in primary care settings to advance the evaluation of acute chest pain.

## Methods

2

This design paper is written according to the Standard for Reporting Diagnostic Accuracy Studies (STARD) 2015 guidelines [12], and according to the Standard Protocol Items: Recommendations for Interventional Trials (SPIRIT) guidelines on defining standard protocol items for clinical trials [13].

### Study design and population

2.1

We designed a prospective diagnostic accuracy trial to evaluate the HEART-GP strategy incorporating point-of-care hs-troponin testing for ruling out MACE in patients presenting with acute chest pain or discomfort in out-of-hours primary care. The trial protocol was prospectively registered in the ISRCTN registry (ISRCTN11954040, https://doi.org/10.1186/ISRCTN11954040) and approved by the CCMO (CIV-NL-22-11-041231, 11-03-2022) and by the Medical Research Ethics Committee of the Amsterdam UMC (NL82428.000.22, 02-03-2023).

Consecutive patient enrollment commenced in March 2023 and has been rolled out since then across four OOH-PC regions in the Netherlands: Alkmaar, Amersfoort, Leiderdorp and Venlo. Together, these regions serve approximately 1 million patients (Fig. 1). Eligible patients are adults (≥18 years) who contact one of the participating OOH-PC centers regarding acute-onset chest pain or discomfort, and are triaged for a face-to-face GP consultation. Patients with signs of hemodynamic instability or chest pain following substantial trauma were excluded since both mandate immediate transfer to the ED and prohibit participation. A complete overview of the trial is displayed in Fig. 2.

**Fig. 1 fig1:**
[figure not shown]
*Healthcare service area of out-of-hours primary care centers in Alkmaar/HONK* (253.000 inhabitants)*, Amersfoort/Eemland* (386.000 inhabitants)*, Leiderdorp/LIMES* (90.000 inhabitants) *and Venlo/Cohesie* (247.000 inhabitants)*, The Netherlands*.

**Fig. 2 fig2:**
[figure not shown]
HEART-GP: patient flow, inclusion procedure and follow-up The upper part depicts the out-of-hours workflow for patients presenting with chest pain within the Dutch healthcare system outside of office hours. The lower part (yellow) outlines the HEART-GP study workflow, including the index consultation and subsequent follow-up procedures.

### Study intervention

2.2

#### HEART-GP strategy incorporating hs-troponin testing (index test)

2.2.1

The intervention involves the HEART-GP strategy (Fig. 3), which combines a single point-of-care high-sensitivity troponin measurement, with clinical assessment and optional ECG. We use the Siemens Atellica VTLi hs-troponin POCT to measure hs-troponin levels from a fingerstick blood sample, which returns results within 8 min. For ethical reasons, the GP is not blinded to the hs-troponin results during the consultation. The specifics of this assay are described elsewhere in further detail, but in essence the whole blood Limit of Detection is 1.6 ng/L and the Limit of Quantitation at 10% CV is 8.9 ng/L [14]​. The non-sex specific 99th percentile upper reference limit for this assay is 22.9 ng/L [15]. In our study we applied a lower decision threshold of ≥4 ng/L for rule out purposes, as evidence from prior studies show a sensitivity of 98.8% and a NPV of 99.8% for ruling out ACS in low-risk populations at the emergency department (ED) [11,15].

**Fig. 3 fig3:**
[figure not shown]
HEART-GP strategy GP: general practitioner, hs-cTnI: high-sensitivity cardiac troponin, POCT: point-of-care test, ACS: acute coronary syndrome.

All (triage) nurses at the participating OOH-PC centers receive standardized training by study personnel to ensure correct execution of the POCT, including sample collection, device operation, and interpretation of results. In the event of a test error, nurses are instructed to repeat the measurement using a maximum of two cartridges. A detailed testing protocol is included in Appendix 1.

The *HEART-GP strategy* guides decision-making on whether to refer the patient to the (cardiac) ED or manage them in primary care. As part of this strategy, it is of importance to note that the GPs' clinical judgement is paramount in deciding on the treatment plan. For instance, even if a patient's hs-troponin POCT value is below the cut-off of 4 ng/L, based on the discretion of the GP the patient may still be referred.

#### Symptom assessment form

2.2.2

The treating physician is asked to complete a structured, symptom-based checklist designed to standardize and document clinical assessment. The form includes symptom elements of three risk scores, namely (modified) H(E)ART, INTERCHEST and the Marburg Heart Score (Table 1). In addition, GPs are asked to record their ‘gut feeling/sense of alarm’, as well as whether they would have referred the patient based on their clinical judgement without access to the POCT result. The checklist is completed during the index consultation, instructed to be completed prior to disclosure of troponin result, to ensure unbiased responses. The form contains no recommendations or prompts regarding management decisions.

**Table 1 tbl1:** (Modified) HEART(s), Marburg Heart Score, INTERCHEST risk stratification scores.

(Modified) HEART score [16,17]		Points	Marburg Heart Score [18]		Points	INTERCHEST [19]		Points
History	Highly suspicious	2	Sex/age (Female ≥65, male ≥55 years)	Yes	1	Sex/age (Female ≥65, Male ≥55 years)	Yes	1
	Moderately suspicious	1		No	0		No	0
	Slightly suspicious	0						
ECG	Significant ST deviation	2	History of cardio-vascular disease	Yes	1	History of coronary artery disease	Yes	1
	Non-specific repolarization abnormalities	1		No	0		No	0
	Normal	0						
Age	≥65 years	2	Patient assumes the pain is of cardiac origin	Yes	1	Chest pain related to effort	Yes	1
	45 – 64 years	1		No	0		No	0
	<45 years	0						
Risk factors	History of atherosclerotic disease or ≥ 3 RF	2	Pain gets worse with exercise	Yes	1	Pain reproducible by palpation	Yes	Minus 1
	1 – 2 RF	1		No	0		No	0
	No known RF	0						
Troponin∗	≥23 ng/L (99th percentile)	2	Pain is not reproducible by palpation	Yes	1	Physician initially suspected a serious condition	Yes	1
	4-23 ng/L	1		No	0		No	0
	<4 ng/L	0						
∗Sex-specific HEARTs: sex-specific 99th percentile for troponin (male 27 ng/L, female 18 ng/L) [15]						Chest discomfort feels like pressure	Yes	1
							No	0

Table 1: *ECG: electrocardiogram, RF: risk factors for atherosclerosis, HEART: History, ECG, Age, Risk Factors, Troponin, INTERCHEST: international chest pain prediction*.

Non-specific repolarization abnormalities: LVH: left ventricular hypertrophy, LBBB: left bundle branch block or PM: pacemaker.

Risk factors: Hypertension, Hypercholesterolemia, Diabetes Mellitus, obesity (BMI >30 kg/m2), smoking, positive family history.

History of atherosclerotic disease: prior Myocardial Infarction, Transient Ischemic Attack, Cerebrovascular accident, Peripheral Arterial disease or previous Percutaneous Coronary Intervention or Coronary Bypass graft.

Textbox 1Out-of-hours primary care in the NetherlandsIn the Dutch healthcare system, GPs serve as round-the-clock gatekeepers to secondary care, except in emergencies requiring immediate ambulance assistance and transport to the ED. OOH-PC centers operate from 17.00 to 08.00 on weekdays and throughout weekends and holidays. They are organized through regional GP cooperatives, serving patients registered with affiliated practices within a defined geographic area (Fig. 1).Upon contact with an OOH-PC center, trained triage nurses, supervised by GPs, conduct telephone triage using the Netherlands Triage Standard (NTS), a standardized, symptom-driven protocol that assigns an urgency level to each case [20]. Although the NTS provides a structured framework, triage nurses or supervising GPs may adjust the final urgency classification based on additional contextual information. This can include the patient's perceived level of distress or whether there were repeated calls for the same symptom within a short timeframe.Patients classified as high urgency are referred directly to the ED without GP assessment. Those with the lowest urgency level receive self-care advice, or are advised to contact their own GP during regular office hours. Patients triaged as intermediate urgency are assessed by a GP at the OOH-PC facility, where they may be treated on-site, referred to the ED for further evaluation, or discharged with appropriate safety-netting advice [21].Alt-text: Textbox 1Textbox 2Why we use major adverse cardiovascular events (MACE)The primary outcome of MACE, a composite of ACS, urgent revascularization, or all-cause death/mortality at 6 weeks follow-up, is an outcome that is patient-centered, objective, and delayed, serving as a suitable reference standard in urgent primary care where not all patients undergo the same in-hospital diagnostic work-up. Using MACE rather than ACS avoids circularity with the index diagnosis and reduces verification bias. It provides a comprehensive and clinically meaningful measure of cardiovascular risk, enhances statistical power, and aligns with established regulatory and methodological standards. All events will be adjudicated with blinding to the index test, with prespecified sensitivity analyses, on the individual components of MACE, performed.Alt-text: Textbox 2

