
### Reference standard (occurrence of MACE)

2.3

We use a delayed-type reference test in which our primary clinical outcome is the occurrence of MACE within 6 weeks from the index consultation (see Textbox 2). A 6-week window was selected to enhance comparability with previous research on MACE after presentation with chest pain in Dutch primary care [22]. MACE is a well-established endpoint accepted by regulatory agencies that captures the overall cardiovascular risk rather than focusing solely on one clinical syndrome. MACE is a composite endpoint, consisting of ACS, urgent coronary revascularization and/or all-cause death. ACS is defined as the occurrence of ST-elevation myocardial infarction (STEMI), non-ST-elevation myocardial infarction (NSTEMI), or unstable angina. Secondary outcomes are (I) the occurrence of (non)fatal myocardial infarction (STEMI or NSTEMI), (II) any hospitalization for a cardiovascular cause (e.g. heart failure, atrial fibrillation, aortic pathology, pulmonary embolism) and (III) all-cause death.

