#### Index contact

2.4.1

The study workflow is described in Fig. 2, Fig. 4. In short, during the consultation the patient receives information about the study's objectives, procedures, potential risks and benefits, and decides on their participation. Upon agreement, initial informed consent is obtained by the treating physician, and hs-troponin POCT is conducted by a trained (triage) nurse. While the POCT runs, the GP completes the ‘*chest pain assessment form*’. Subsequently, the GP determines the treatment plan ((e.g. discharge with safety-net advice (‘watchful waiting’), consulting a cardiologist or referral to the hospital for further assessment)). At all times, the GP's own clinical judgement serves as the guiding principle in the management following the consultation. For safety reasons, urgent referral is advised in cases of high clinical suspicion of ACS, hs-troponin POCT values ≥ 4 ng/L, and/or an abnormal ECG (if performed), in line with the HEART-GP strategy recommendations. Additionally, GPs are informed to refer all patients with troponin levels exceeding the overall 99th percentile of 22.9 ng/L. Patients who refuse study participation receive routine care only, which focuses on history taking, physical examination and, based on the discretion of the GP, potentially an ECG, as this is not a part of the standard work-up of chest pain in Dutch primary care [6].

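### Textbox 2 says MACE avoids circularity, but MACE contains ACS, and the unblinded index test steers the work-up that detects it, so sensitivity and NPV are likely biased upward

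*Protocol article*

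**What the plan says.** Textbox 2 (section 2.2.2) justifies the reference standard: "Using MACE rather than ACS avoids circularity with the index diagnosis and reduces verification bias". It gives as a reason that, in urgent primary care, "not all patients undergo the same in-hospital diagnostic work-up".

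Other sections describe the design to which this applies:

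- **Outcome (2.3).** "MACE is a composite endpoint, consisting of ACS, urgent coronary revascularization and/or all-cause death", and "ACS is defined as the occurrence of ST-elevation myocardial infarction (STEMI), non-ST-elevation myocardial infarction (NSTEMI), or unstable angina". The window is six weeks from the index consultation.
- **Blinding (2.2.1).** "For ethical reasons, the GP is not blinded to the hs-troponin results during the consultation".
- **Referral (2.4.1).** "urgent referral is advised in cases of high clinical suspicion of ACS, hs-troponin POCT values" at or above 4 ng/L, and/or an abnormal ECG. Below the cut-off, "based on the discretion of the GP the patient may still be referred" (2.2.1, after Fig. 3).
- **Ascertainment (2.4.2).** Patients are contacted at two weeks, general practice and regional hospital records are searched for everyone, and a panel blinded to the POCT result adjudicates, with a cardiologist as third expert. No common diagnostic test is described for patients who are not referred.
- **Comparator (2.2.2).** The GP records whether he or she would have referred without the POCT result, and is instructed to do so before the result is disclosed.

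**The concern.** A composite that includes ACS inherits any circularity that ACS carries. Section 1.1 says that GP assessment, with or without an ECG, cannot safely rule out ACS, though an ECG may confirm ST elevation. NSTEMI and unstable angina therefore depend largely on hospital work-up for their detection, and the index test influences who receives it.

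A mild event in a strategy-negative patient who stays in primary care enters the data only if somebody diagnoses it within six weeks. If nobody does, a false negative is recorded as a true negative. Both safety measures, sensitivity and NPV, then look better than they are. The trial is meant to support a rule-out claim, and with about 63 expected events that claim rests on very few missed patients. A reader who accepts that circularity has been avoided would see no reason to test for this.

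**Working it through.** **1. The plan's own figure.** Inputs from section 2.6.1: sensitivity 0.98, margin 0.03, two-sided alpha 0.10 (z = 1.645), prevalence 0.07.

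- Events needed = z² × 0.98 × 0.02 / 0.03² = 58.92.
- Participants = 58.92 / 0.07 = 841.7, rounded up to 842.

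This reproduces the stated 842. The sample size is not in dispute; it supplies the 3-point margin and the expected number of events, 900 × 0.07 = 63.

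**2. Effect of undiagnosed events on sensitivity.** Assumptions, since the documents give no such figures: 63 observed MACE, of which one is an observed miss, and k further events among strategy-negative patients that are never diagnosed. Sensitivity = 62 / (63 + k).

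| k | Sensitivity | Share of strategy-negative events never diagnosed |
|---|---|---|
| 0 | 62/63 = 98.4% | 0 |
| 1 | 62/64 = 96.9% | 1/2 |
| 2 | 62/65 = 95.4% | 2/3 |

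Each event costs about 1.5 points, and two cost 3.0. The last column shows what is being assumed: with only one observed miss, even k = 1 means that half of the strategy-negative events were never found.

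**3. The same question without fixing one observed miss.** Let q be the share of strategy-negative events that is diagnosed, with all strategy-positive events diagnosed. Observed sensitivity = Se / (Se + (1 − Se)q).

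| True Se | q = 0.75 | q = 0.5 | q = 0.25 |
|---|---|---|---|
| 98% | 98.5% | 99.0% | 99.5% |
| 95% | 96.2% | 97.4% | 98.7% |
| 90% | 92.3% | 94.7% | 97.3% |

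Under this model the bias is upward for any q below 1. It is small if true sensitivity is already 98%. It matters more if true sensitivity is lower, because 95% can then be reported close to the 98% target.

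**4. NPV.** Assume one observed miss and 450 strategy-negatives (50% of 900). NPV is 449/450 = 99.8%; with two undiagnosed events it is 447/450 = 99.3%. With 270 strategy-negatives (30%) it goes from 269/270 = 99.6% to 267/270 = 98.9%.

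**5. Comparison with GP judgement.** Per 100 true events, let a = positive on both, b = HEART-GP only, c = GP only (diagnosed with probability r), d = neither (diagnosed with probability q). Observed difference in sensitivity = (b − rc) / (a + b + rc + qd). All values are assumed.

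- No event in the GP-only cell (a, b, c, d = 85, 10, 0, 5): the true difference is 10.0 points. Observed, it is 10/97.5 = 10.3 points at q = 0.5 and 10/95 = 10.5 at q = 0. The ratio stays 95/85.
- Events in that cell, half of them undiagnosed (85, 5, 5, 5; r = 0.5; q = 1): the true difference is 0. Observed, it is (5 − 2.5)/97.5 = +2.6 points for HEART-GP.
- The same cells with r = 1: the observed difference is 0 at any q.

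Material bias in the comparison therefore requires events in the GP-only cell that stay undiagnosed.

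**The case against.** The strongest defence has four parts.

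- **The sentence is about the index diagnosis, and it claims only that verification bias is reduced.** The second half stands: all-cause death and a delayed endpoint do lessen dependence on the initial work-up. The first half does not, because nothing in section 2.3 excludes an ACS diagnosed at the index referral from counting as MACE.
- **There are real safeguards.** Patient contact, record search for all participants, blinded adjudication and component analyses (Textbox 2) are planned. They lessen the problem. Blinding prevents biased reading of evidence but cannot supply evidence where no work-up took place, and records contain only what somebody diagnosed.
- **The illustration rests on assumed inputs.** This stands. The only related figure, 8-19% of ACS initially missed (section 1.1), is not a never-diagnosed rate.
- **Sensitivity tables belong in an analysis plan.** Their absence from an article is indeed no fault. The fault is the stated property; the table is part of the remedy.

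A reader might also infer that the comparison with GP judgement is necessarily biased towards HEART-GP. The documents do not support that. High clinical suspicion and an abnormal ECG are themselves referral triggers, and the GP may refer despite a low troponin, so few events may fall in the GP-only cell. Fig. 3, which sets out the strategy, is not shown. For the same reason, a troponin below 4 ng/L cannot be equated with a negative strategy. Against that, referrals can fall relative to the GP's recorded intention only if some patients the GP would have referred are held back. If the efficiency aim succeeds, the cell contains patients; whether it contains events is unknown.

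**Conclusion.** The statement that MACE avoids circularity is wrong as written; the statement that it reduces verification bias is defensible. Sensitivity and NPV of HEART-GP are likely biased upward, by an amount the documents do not allow one to estimate. For scale, each undiagnosed event lowers sensitivity by about 1.5 points, and two use up the 3-point margin. That rests on 63 observed MACE, one observed miss, and complete detection among strategy-positive patients. Referral is advised rather than mandatory, so if some strategy-positive patients also miss work-up and have undiagnosed events, the bias is smaller. Bias in the comparison with GP judgement is possible but not established. This should be corrected; it does not invalidate the design, whose unblinded GP is a declared ethical choice.

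**What to change.** 1. Reword Textbox 2 to say that the composite and delayed follow-up reduce, but do not remove, circularity and differential verification.
2. Pre-specify, in the protocol or the analysis plan, a tipping-point table: the number of undetected MACE among non-referred, strategy-negative patients at which sensitivity, NPV and the paired HEART-GP minus GP difference cross stated values.
3. Report results by actual referral status, and for the components less dependent on index work-up: death, STEMI and urgent revascularization.

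A Begg-Greenes or inverse-probability correction need not be required. Every patient has the delayed reference, so the issue is uneven detection rather than a missing reference result, and few events among referred strategy-negative patients would inform it. Repeating the comparison on MI or death would not cure the problem either: it keeps NSTEMI, and both outcomes are already secondary outcomes in section 2.3.

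The cost is a little extra analysis on data already collected, and a more cautious safety statement. The component results will rest on fewer events and be less precise.
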